### 2.8. Data Analysis

For the statistical analysis, all variables will be coded by using IBM Statistics SPSS v.21 software (Chicago, USA) for Windows and revised twice. A protocol approach will be followed where missing data will not be included in the analysis.

All descriptive statistical parameters will be expressed as absolute (‘n’) and relative (‘%’) frequencies for each qualitative variable category. Quantitative variables will be analysed with the mean, median, and standard deviation to observe their behaviour at a confidence interval of 95%. Normal variable distribution will be analysed by using the Kolmogorov–Smirnov test with Shapiro–Wilk correction. 

A repeated measures ANOVA will be used to compare mean differences between the intervention and control groups over time, considering the time–group interaction effect. The size of the effect will be analysed based on Cohen’s d [40]: 0–0.3 low, >0.3–0.8 moderate, and >0.8 large effect size. Any incomplete questionnaires will be excluded from the analysis. Results will be considered statistically significant when *p* < 0.05.

The PROCESS macro will be used to examine the mediating effects of sleep quality on the relationship between attending the sleep intervention or not. This analysis uses linear regression to estimate indirect effects according to Hayes and Rockwood’s methods recommended for clinical studies and focuses on two measurement moments [41]. Post-treatment scores will be added as mediators, and baseline scores for the outcome variables and mediators will be added to the models as covariates. Least-square path analysis will be used and the bootstrap confidence interval (5000 permutations) will be applied to estimate indirect effects.

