## Abstract

We develop a protocol for assessing the impact of an intervention aimed at improving sleep quality among university nursing students. The study is designed as a pilot randomized controlled trial to be applied during the 2022-23 academic year and is registered at Clinical Trials Gov website (NCT05273086). A total of 60 nursing students will be recruited from a Spanish university. They will be divided into two groups: (30) intervention group and (30) control group. The intervention group will attend two cognitive–behavioural therapy sleep programme sessions focused on knowledge of anatomical structures involved in sleep, chronotype, synchronization, and good sleeping habits. Subjective and objective sleep quality will be assessed before and after the intervention for both groups. In addition to sleep quality, socio-demographic parameters, physical activity, lifestyle habits, and anthropometric measures will be considered prior to intervention. Finally, a satisfaction questionnaire will be applied for posterior analysis. This study is an innovative, relevant intervention that aims to improve sleep quality among university nursing students. Both the approach and the use of objective and subjective validated outcome measurements are key features of this study.

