#### 2.3.3. Sample Size Calculation

For a population size of 70, at least 60 samples are required to have a confidence level of 95% so that the real value is within ±5% of the measured/surveyed value. For two-group comparisons, at least 60 samples are required for an expected medium effect [33].

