### 2.6. Ethical Considerations

This study will be conducted according to the principles established in the Declaration of Helsinki, in the Convention on Human Rights and Biomedicine (Oviedo Convention), and in the UNESCO Universal Declaration on the Human Genome and Human Rights. This study has been approved by the Research Ethics Committee of Camilo José Cela University (code: 06-22-UCJC-Sleep). 

All participants will be informed of the duration and characteristics of the study, and of its voluntary nature. After receiving a detailed explanation of the project, any doubts raised by participants will be answered before the students are asked to sign the informed consent form, which mandatorily must be signed to participate.

Participants may abandon the study at any time, with no further consequences. The highest professional conduct and absolute confidentiality will be always maintained, in accordance with European Regulation (EU) 2016/679 on the protection of natural persons and data processing and free movement, the Framework Act 3/2018 on personal data protection and the guarantee of digital rights, and Act 14/2007 on biomedical research. Only the principal researcher of the project will have access to the codified database.

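### The stated main analysis leaves out students with missing data under a protocol approach, so it may not estimate the effect of being assigned to the programme

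*Protocol article*

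**What the plan says.** Section 2.8 (Data Analysis) sets the rule for who is analysed: "A protocol approach will be followed where missing data will not be included in the analysis". Further on it adds: "Any incomplete questionnaires will be excluded from the analysis". The main comparison is also fixed there: "A repeated measures ANOVA will be used to compare mean differences between the intervention and control groups over time", with the time-by-group interaction as the effect of interest.

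Other sections show how data can go missing:

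- **Withdrawal.** Section 2.6: "Participants may abandon the study at any time, with no further consequences".
- **Blinding.** Section 2.3.5 blinds the analysts only. Students and facilitators know the allocation.
- **Sessions.** Sections 2 and 2.4 give sessions to the intervention group alone.
- **Measurement.** Section 2.5.1 asks every student in both arms for two seven-day periods of device wear and two completions of the 19-item PSQI.

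The article does not mention an analysis of all students as randomised, imputation or a sensitivity analysis. The abstract plans 60 students, 30 per arm.

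**The concern.** Randomisation makes the two arms comparable only while everyone randomised is counted in the arm assigned. Leaving students out for reasons that arise after allocation gives up that protection. If the reasons differ by arm and are linked to how sleep changes, the difference between arms partly reflects who was left in.

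This design is open to that. Allocation is known, one arm is offered a programme and the other nothing, and non-attendance is possible in one arm only. The discussion (section 3) relies on the controlled design for evidence of effectiveness and expects the results to support funding for a larger study. A distorted estimate would therefore carry over into the next trial's planning.

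**Working it through.** **1. What the rule excludes, on each reading.** The article writes of a protocol approach, without the word per. The two readings differ for one kind of student:

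| Student | Per-protocol reading | Narrow reading (missing data only) |
|---|---|---|
| Attends, both assessments complete | in | in |
| Misses sessions, both assessments complete | out | in |
| No post assessment | out | out |
| Incomplete PSQI | out for the PSQI | out for the PSQI |

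The last two rows follow from section 2.8 on either reading. The second row depends on the reading, because no attendance threshold is written.

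**2. What the ANOVA adds.** With two time points, the time-by-group interaction is the difference between arms in mean change (post minus pre). A student lacking either value has no change score and is dropped, so a missing post week also discards the baseline week. A stable difference in level between students kept and students lost cancels in the change. Bias needs a difference in *change*.

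**3. Size, under stated assumptions.** The article gives no rate of loss, so these inputs are assumed. Let the retained students of the intervention arm have mean improvement m. Let a share q be excluded, who would have improved by m − delta (in SD of the change).

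- Mean of the whole arm: (1 − q)·m + q·(m − delta) = m − q·delta.
- Mean of those analysed: m.
- Bias in the arm mean: m − (m − q·delta) = **q·delta**.

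With no exclusions in the control arm, the bias in SD is:

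| | q = 10% | q = 20% | q = 30% |
|---|---|---|---|
| delta = 0.5 | 0.05 | 0.10 | 0.15 |
| delta = 0.8 | 0.08 | 0.16 | 0.24 |

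Here delta is measured against the rest of the arm. Measured against the whole-arm mean, the expression would be q·delta/(1 − q), for example 0.20 × 0.5 / 0.80 = 0.125.

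**4. Both arms.** If the control arm also loses students, the bias in the contrast is q(I)·delta(I) − q(C)·delta(C). Some cases:

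- 20% and 0.5 in both arms: 0.10 − 0.10 = 0.
- 20% and 0.5 in the control arm only: 0 − 0.10 = −0.10, against the programme.
- delta = 0 in both arms: no bias, whatever the loss.

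**5. The count of 60.** Section 2.3.3 sets 60 as the minimum for a population of 70 at ±5%. With an assumed proportion of 0.5, this reproduces: 1.96² × 0.25 / 0.05² = 384.1, and 384.1 / (1 + 383.1/70) = 59.3, rounded up to 60. The abstract plans exactly that number, so one exclusion leaves 60 − 1 = 59. Nothing further follows for this point.

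**The case against.** **The text does not say per-protocol.** The clause after the word approach concerns missing data, not attendance, and no section excludes a non-attender who completes both assessments. This stands in part. Per-protocol is the most natural reading, but a reader who infers an attendance rule goes beyond the text. The complete-case rule needs no inference.

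**The direction of bias is not shown.** Both arms carry the same device and questionnaire load, and control students who are offered nothing may also drop out. That excluded students might sleep worse is a statement about level, which cancels in the interaction test. This stands. A reader might infer that the effect will be inflated; the documents do not support that. Exclusions that favour the programme are plausible, and step 4 shows that other patterns give zero or the opposite sign.

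**The 60 and the power are separate matters.** A reader might infer that the rule takes the trial below its minimum or costs it material power. It falls below 60 only if someone is lost. A mixed model with two time points cannot supply missing post values, so the fix does not restore 60 complete pairs. The article gives neither a numeric effect nor a power from which to price the loss.

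**A questionnaire rule is not a student rule.** Section 2.8 does not say that an incomplete PSQI removes that student's device outcomes. That is correct; the fix only makes it explicit.

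**It is a condensed article on a pilot.** Sensitivity analyses are often left to the full plan, so their absence here proves nothing. That is fair, but the objection is to the rule the article does state. Pilot status lowers the stakes without removing them, since section 2.8 plans significance tests and effect-size grading.

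**Conclusion.** The point holds as a criticism of a stated rule. Section 2.8 selects students for analysis by what happens after randomisation, in a trial where students are unblinded and only one arm has sessions to attend. If exclusions differ by arm and relate to change in sleep, the result does not estimate the effect of assignment.

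The size and direction are not known from the documents. For exclusion in the intervention arm only, the four combinations of 10% and 0.5, 20% and 0.5, 30% and 0.5, and 20% and 0.8 give 0.05 to 0.16 SD; the corner at 30% and 0.8 gives 0.24 SD. All of these are illustrations that rest on assumed shares and differences and on no comparable loss among controls.

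The per-protocol label is a reading, though the natural one. On sample size, the documents support only that any loss leaves fewer than the stated 60.

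**What to change.** Replace the two exclusion sentences in section 2.8 with text to this effect:

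> The main analysis includes all randomised students in the group assigned, whatever their attendance, using all available pre and post values in a linear mixed model with group, time and their interaction. Post measurements are sought from students who stop attending sessions but have not withdrawn consent. A complete-case per-protocol analysis, with its attendance criterion defined beforehand, is a sensitivity analysis. An incomplete questionnaire is excluded only from the score that cannot be computed from it.

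The mixed model is one suitable choice. It is valid if data are missing at random and does not remove bias from losses that depend on unobserved change, so obtaining the post measurements matters more than the model.

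**Cost.** One paragraph and some follow-up effort. The mixed procedure is in the SPSS package already named, and no new instrument is needed. The estimate may be slightly smaller because non-attenders count.

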#### 2.3.4. Randomization

An independent researcher who is unaware of the study characteristics will conduct the random assignment procedure. A computer-generated random number sequence (Sealed Envelope™ software version 1.21.0, London, UK), assigned to participants’ academic record number will be used to randomly designate participants to one of the two groups (IG or CG). Random permuted blocks will also be used to reduce the random sequence predictability and guarantee a 1:1 ratio. This sequence will be password-protected in a table and will be hidden from other researchers during the study.

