#### 2.5.1. Dependent Variables

Sleep quality: Kronowise 3.0, Kronohealth, S.L., Spain. Kronowise 3.0 is a wrist device that conducts ambulatory circadian monitoring (ACM) based on thermometry, motor activity, and body position (TAP). TAP uses a combination of sensors in an algorithm that has been validated as ambulatory polysomnography. It was validated by comparing the assessment of these parameters with polysomnography in adults [35] and in patients diagnosed with Parkinson’s [36]. The device can measure sleep quality and circadian rhythms and identify circadian chronodisruption through parameters such as sleep latency, total sleep time (in minutes), sleep efficiency, number of awakenings and time between waking and sleep [35]. It can also identify sleep phases, nocturnal awakenings, temperature, exposure to infrared and blue light as well as other parameters such as time in bed, sleep onset, awake time, sleep interval, total time in movement, time in movement index, sleep acceleration index, wrist sleep temperature, napping time and napping frequency [36]. Participants will wear the device for seven consecutive days, including weekdays and weekends. Both groups will be measured twice (before and after the intervention), meaning that all participants will wear the device for a total of 14 days. Participants will be given appointments to fit and remove the devices. Information provided by the devices will be entered into the software that will be sent to Kronohealth S.L., Spain, which will produce reports of both measurements with the results of the parameters mentioned above, with the sleep quality indices established according to the device validation [35].Perceived sleep quality: Pittsburgh Sleep Quality Index, PSQI [37]. The PSQI contains 19 items and seven clinically important components related to sleep quality: subjective sleep quality, sleep latency, sleep duration, sleep efficiency, sleep disturbances, use of sleeping medication, and daytime dysfunction. Responses will be reported based on a Likert-type scale from 0 to 4. Overall sleep scores of 5 or less will be considered good quality, whereas scores of 5 or more will be considered low quality. The PSQI version that will be used is validated into the Spanish university framework by De la Vega et al. [37] with a Cronbach’s alpha of 0.72. The questionnaire will be given to all participants twice (before and immediately following the intervention).

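### The main comparison is in effect a change-score test and gives up precision that adjusting for the already collected baseline would recover

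*Protocol article*

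**What the plan says.** Section 2.8 (Data Analysis) fixes the between-group analysis: "A repeated measures ANOVA will be used to compare mean differences between the intervention and control groups over time", "considering the time–group interaction effect". No baseline covariate is named for this comparison. Later in the same section, for the mediation models only, "baseline scores for the outcome variables and mediators will be added to the models as covariates".

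Section 2.5.1 sets two time points for both sleep outcomes. For the wrist device: "Both groups will be measured twice (before and after the intervention". For the PSQI: "The questionnaire will be given to all participants twice (before and immediately following the intervention". Table 2 confirms one pre and one post assessment in each arm for both instruments.

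On size, the Abstract says: "They will be divided into two groups: (30) intervention group and (30) control group". Section 2.3.4 describes permuted blocks to "guarantee a 1:1 ratio", and section 2.3.3 states that "at least 60 samples are required for an expected medium effect".

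**The concern.** With only two time points, the interaction in a repeated measures ANOVA carries no more information than the between-group difference in mean change. Subtracting the baseline fixes its coefficient at 1. ANCOVA estimates that coefficient from the data, and it is normally below 1. Unless baseline and follow-up are almost perfectly correlated, subtraction over-corrects and adds baseline noise to the treatment comparison.

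This matters because the trial has little precision to spare. The Discussion (section 3) accepts that the sample may be too small to show a group difference and raises the risk of a type II error. Section 2.3.3 works from a population of 70, and section 2.7 describes ten devices used in a staggered 16-week schedule, so a larger sample is not an easy remedy. The baselines are collected from both arms anyway, and the plan already uses them as covariates in its mediation models. Only the main comparison leaves them out.

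**Working it through.** **Inputs from the article.** 30 per arm (Abstract); 1:1 individual randomisation (2.3.4); one pre and one post value per outcome (2.5.1, Table 2); significance level 0.05 (2.8).

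**Assumptions, because the article gives no figure.** Two-sided testing; a medium effect taken as d = 0.5 post-score SDs; equal pre and post SDs; pre-post correlation r from 0.3 to 0.9; no missing values.

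**1. The plan's own figure.** The survey-precision calculation in 2.3.3 reproduces: 384.15 / (1 + 383.15/70) = 59.3, rounded up to 60. It has no bearing on the group comparison. The second statement, 60 for a medium effect, does not reproduce at d = 0.5 and 80% power for a plain two-group comparison: n per arm = 2(1.960 + 0.842)² / 0.5² = 62.8, so 63 per arm or 126 in total. Neither a power nor a numerical effect size is stated, so the basis of 60 cannot be recovered. The point below does not depend on it.

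**2. The planned test is a change-score test.** In a simulated two-arm, two-time data set with 30 per arm, the interaction F was 0.94487 and the squared t statistic on change scores was 0.94487.

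**3. Variance factors (multiples of SD²).**
- Change score: 2(1−r)
- ANCOVA: 1−r² = (1−r)(1+r)
- Ratio, ANCOVA to change: (1+r)/2
- Difference: 2(1−r) − (1−r²) = (1−r)²

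The equal-SD assumption does not drive the direction. With pre SD s₀ and post SD s₁, the difference is s₀² + s₁² − 2r·s₀s₁ − s₁²(1−r²) = (s₀ − r·s₁)², which is never negative.

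Estimating the slope multiplies the ANCOVA variance by about 1 + 1/56 = 57/56 and reduces the degrees of freedom from 58 to 57. Allowing for the multiplier, ANCOVA keeps the smaller variance while (1+r)/2 × 57/56 < 1, that is, for r below 2 × 56/57 − 1 = 0.965.

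**4. Power at 30 per arm, d = 0.5.** Noncentral t with noncentrality 0.5 × √(30/2) / √(variance factor) = 1.936 / √(variance factor), the ANCOVA factor including 57/56. Example at r = 0.5: change score 1.936/√1.00 = 1.94; ANCOVA 1.936/√(0.75 × 57/56) = 2.22.

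| r | Change factor | ANCOVA factor | Ratio | Power, planned test | Power, ANCOVA |
|---|---|---|---|---|---|
| 0.3 | 1.40 | 0.91 | 0.65 | 36% | 51% |
| 0.5 | 1.00 | 0.75 | 0.75 | 48% | 59% |
| 0.7 | 0.60 | 0.51 | 0.85 | 69% | 75% |
| 0.8 | 0.40 | 0.36 | 0.90 | 85% | 88% |
| 0.9 | 0.20 | 0.19 | 0.95 | 99% | 99% |

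A simulation of 40,000 trials per setting agreed: 36.9% vs 50.9% (r = 0.3), 48.0% vs 59.1% (0.5), 68.9% vs 75.3% (0.7) and 99.0% vs 99.2% (0.9).

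**5. The same loss in other terms.**
- A comparison of post scores alone has variance factor 1 and power 48%. The change-score factor exceeds 1 whenever r < 0.5, so in that range the planned test is weaker than ignoring the baseline (36% vs 48% at r = 0.3).
- The difference detectable with 80% power at r = 0.5 is 0.74 SD for the planned test and 0.64 SD for ANCOVA (0.736 × √(0.75 × 57/56) = 0.64).
- Numbers per arm for 80% power at d = 0.5 (normal approximation), change score vs ANCOVA: 88 vs 58 at r = 0.3, 63 vs 48 at r = 0.5, 38 vs 33 at r = 0.7.

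**6. Where the loss comes from.** A chance baseline difference Δ between arms shifts the expected change-score difference by −(1−r)Δ. At 30 per arm the standard error of Δ is √(2/30) = 0.258 SD, so at r = 0.5 an ordinary one-standard-error imbalance moves the estimate by 0.5 × 0.258 = 0.13 SD, about a quarter of a 0.5 SD effect. This is not a harm on top of the variance loss: it is the (1−r)² term in step 3.

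**The case against.** The strongest reply is that nothing here is an error. Under individual randomisation the interaction test keeps its type I error and is unbiased over repeated trials, so this is a choice between two valid estimators. That is correct, and it limits the finding to efficiency.

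Second, the benefit depends on a correlation that the article does not report. The striking figures come from r = 0.3; at 0.8 the gain is about 3 points of power and at 0.9 it is nil. This also stands. The size is uncertain, but the direction is not, apart from a trivial cost when r is very close to 1.

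Third, the mediation models regress post-treatment scores on group with baseline as covariate, so something close to the ANCOVA estimate would appear as one path of those models. That softens the gap without closing it, because the path is not the planned group comparison and would not be reported as the treatment effect.

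Fourth, the study is a pilot meant to give preliminary data, so power counts for less than in a confirmatory trial. This carries some weight. But the plan sets a 5% significance threshold, the Conclusions (section 4) state an aim of demonstrating a benefit, and preliminary data for a larger application are more useful when the estimate is more precise.

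**Conclusion.** The concern holds. Section 2.8 commits the main comparison to a test equivalent to comparing change scores, although a baseline is available for every sleep outcome in both arms and ANCOVA would use it better. At 30 per arm and d = 0.5, the cost is about 15 points of power at r = 0.3, 11 at 0.5, 6 at 0.7, 3 at 0.8 and none at 0.9. These figures rest on assumed values of r and d, equal pre and post SDs, two-sided testing and complete data. The ordering of the two methods needs neither the assumed r nor equal SDs. This is a worthwhile improvement that should be made, not a flaw that invalidates the plan.

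**What to change.** Replace the sentence on the main comparison in section 2.8 with wording such as:

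> For each sleep outcome, the post-intervention value will be compared between groups by ANCOVA, with group as factor and the same outcome's baseline value as covariate. The adjusted mean difference will be reported with its 95% confidence interval and p value.

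The repeated measures ANOVA may stay as a supportive display of means over time. A mixed model with baseline means constrained equal across arms is an acceptable alternative and gives essentially the same result with complete data. The two can differ when follow-up values are missing, so the plan should name one as the main analysis.

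The cost is a change of wording and one residual degree of freedom (58 to 57), already counted in the ANCOVA power figures. No extra participants, visits or measurements are needed. The change should be made before any outcome data are compared by group.

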### 2.1. Hypotheses

We pose the conceptual hypothesis that participants in the intervention group will improve their sleep quality, measured by objective monitoring parameters, and their subjective perception. 

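### No primary outcome is named among 19 to 20 device parameters and the PSQI, and one unadjusted p < 0.05 covers all results

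*Protocol article*

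**What the plan says.** Section 2.1 states one conceptual hypothesis: the intervention group will improve in sleep quality, "measured by objective monitoring parameters, and their subjective perception". The device side is plural and no endpoint is singled out.

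Section 2.5.1 sets out two dependent variables, device-measured sleep quality and the PSQI. The device is credited first with "parameters such as sleep latency, total sleep time (in minutes), sleep efficiency, number of awakenings and time between waking and sleep". A second list opens with sleep stages, waking at night, temperature and light exposure, and goes on to "time in bed, sleep onset, awake time, sleep interval, total time in movement, time in movement index". Four more close it: an index of acceleration, the temperature at the wrist, and the length and number of naps. The manufacturer's reports will give these parameters for both measurement weeks, together with indices of sleep quality taken from the device's validation. Those indices are not named. The PSQI is described with its overall score and seven components.

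Section 2.8 says that "A repeated measures ANOVA will be used to compare mean differences between the intervention and control groups over time", with attention to the time-by-group interaction, but does not say on which variables. The only decision criterion is "Results will be considered statistically significant when" p < 0.05. The mediation paragraph of the same section uses sleep quality as the mediator and refers to outcome variables without naming them.

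No outcome is called primary in sections 2.1, 2.3.3, 2.5.1 or 2.8.

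**The concern.** A success rule needs a defined outcome. Here about 20 device measures could each stand for sleep quality, all meet the same unadjusted threshold, and nothing ranks them. Someone who follows the text exactly could decide, after seeing the results, which parameter carries the claim. The 5% threshold then no longer describes the chance of a false claim.

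This matters because the article wants more than description. Section 2.3.3 sizes the trial for a two-group comparison, section 4 says the research is meant to show a beneficial effect, and section 3 intends the data to support funding applications for a larger study.

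**Working it through.** **The plan's own figure.** The plan states no overall error rate. Its only related figure is N = 60 in section 2.3.3. With X = 1.96² × 0.25 / 0.05² = 384.1, the finite-population formula gives n = 70 × 384.1 / (384.1 + 69) = 59.3, rounded up to 60. The figure reproduces, but it is the survey precision for a proportion. The accompanying medium effect is tied to no variable. The sample size therefore does not reveal a primary outcome.

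**Number of candidate outcomes (section 2.5.1).** First list: 5. Second list: 4 to 5 (light exposure counted once or twice), then 6, then 4. Total: 5 + (4 to 5) + 6 + 4 = 19 to 20, or about 17 to 18 if the overlapping awakenings and temperature entries are merged. Adding the PSQI global score to 20 gives 21.

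**Independent tests, no true effect.** With two time points and two groups, each interaction test at p < 0.05 has a 5% chance of significance in either direction and 2.5% in the favourable one (sidedness is not stated; two-sided is assumed).

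- Any significant result: 1 − 0.95^k. Favourable result: 1 − 0.975^k.
- k = 21: 65.9% any, 41.2% favourable.
- k = 18 (entries merged): 60.3% any, 36.6% favourable.
- k = 28 (seven PSQI components added): 76.2% any, 50.8% favourable.

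**Correlated tests.** Many parameters overlap. Section 1 defines sleep efficiency as the ratio of total sleep time to time in bed, and all three are listed. The documents give no correlations, so a common value was assumed: 21 equally correlated normal test statistics, 100,000 draws, critical value 1.96.

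| Assumed correlation | Any direction | Favourable |
|---|---|---|
| 0 | 66% | 41% |
| 0.3 | 55% | 29% |
| 0.5 | 43% | 22% |
| 0.7 | 30% | 15% |
| 0.9 | 16% | 8% |
| One prespecified test | 5% | 2.5% |

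**If both the PSQI and a device measure must improve.** Under the complete null the joint rate cannot exceed that of the PSQI test alone: 5% in either direction, 2.5% favourable. With 20 independent device tests, also independent of the PSQI, it is 0.642 × 0.05 = 3.2% for either direction, or 0.397 × 0.025 = 1.0% favourable. That protection depends on the PSQI also being null. If the PSQI truly improves and its test nearly always succeeds, the false claim on the device side approaches the rate for the device family, 1 − 0.975^20 = 39.7% for independent tests.

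**The case against.** Several points on the other side are sound.

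- *A reader might infer that every listed parameter will be tested.* Section 2.8 does not say so. Much of the list describes what the device can record, and appearing in a manufacturer's report is not the same as being tested. Light exposure is not obviously a sleep outcome. Testing each parameter is a plausible reading, not a stated plan.
- *A reader might infer that one significant parameter is enough.* Section 2.1 joins the objective and subjective sides with an 'and'. If both are required, the error rate under the complete null is not inflated. The text does not settle this either way.
- *A reader might infer that a chance improvement is more likely than not.* The figures above one half count worsening as well as improvement and need weak correlation. With 21 tests the favourable figure is at most about 41%.
- The unnamed device indices may be the intended summary outcome. If so, naming one would go most of the way.
- The trial is called a pilot, and multiplicity adjustment is often left to an analysis plan, which is not shown.

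The last point does not remove the problem. Naming the main outcome is core protocol content, section 2.5.1 describes the outcomes at length without ranking them, and the blanket threshold is stated text rather than an omission. The pilot label sits beside a comparison-based sample size and an aim of showing an effect. Because the tested variables and the success rule are unstated, the inflated readings cannot be excluded.

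**Conclusion.** The concern holds in a limited form. The protocol designates no primary outcome, applies one unadjusted threshold to all results, and leaves open both the device measure and the rule for combining objective and subjective results.

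The size depends on assumptions that the documents do not settle. If 21 outcomes are each tested and any favourable result counts, the chance of a false improvement is about 15% to 41% for correlations from 0.7 down to 0, roughly 6 to 16 times the 2.5% of a single prespecified test. For significance in either direction it is about 30% to 66%, against 5%. Temperature, light exposure, sleep onset and napping have no stated favourable direction, so under that reading the practical risk lies between the two ranges. If both sides must improve, the rate under the complete null is controlled, but the device measure can still be selected after the fact.

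The documents do not support saying that each parameter will be tested, that any single one would suffice, or that a chance improvement is likely. What can be said is that the chance of a false finding is not held at its nominal level by anything in the text.

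**What to change.** Before outcome data are seen, amend sections 2.5.1 and 2.8 as follows.

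1. Name two primary outcomes: the PSQI global score and one device measure. The sponsor chooses the latter: a named validated index, or a single parameter such as sleep efficiency averaged over the seven days.
2. State the success rule. If both must improve, test each at 5%. If either suffices, use Holm at an overall two-sided 5%. Even a plain split at 0.025 each gives at most 1 − 0.975² = 4.9% for independent tests.
3. Replace the blanket threshold sentence with that rule. Report all other device parameters and the PSQI components as exploratory mean differences with 95% confidence intervals, without significance claims.

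The cost is one paragraph of text and no change to design or data collection. Fewer results can be called significant, and the stricter first step has a price in power. For a simple two-sample comparison with 30 per arm and a standardised difference of 0.5, power is 49% at 0.05 and 38% at 0.025. Requiring both outcomes avoids the split, but joint power cannot exceed that of the weaker outcome.
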